### 3. Study Design

This study is a randomized controlled trial (RTC) with blinding of the participants and blinding of all raters. ADHD adults will be blindly allocated to one of the following two groups by a restricted randomization technique (see recruitment section):

1. fMRI-neurofeedback training, feedback from dorsal anterior cingulate cortex (n=10)
2. fMRI-neurofeedback training, feedback from control brain region (n=10)

Each group will receive the same screening, pre- and post-assessment and 6 fMRI-neurofeedback training sessions. The duration of each fMRI-neurofeedback training session will be approximately 75 minutes. The frequency will be weekly sessions. The duration of the experiment for each participant from the selection until the last session will be approximately 9 weeks.

The control group will receive exactly the same as the fMRI-neurofeedback group, except for the feedback. The control group will receive feedback from a control brain region, which will be selected such that it is activated by different tasks than the dorsal anterior cingulate cortex. This selection will be made based on literature research, previous data, and data from an ongoing pilot experiment.

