### Randomization procedure

Balancing potential confounding factors is of special importance in a study with a sample size as small as the proposed study. To achieve this we will apply a restricted randomization technique called sequential balancing, a form of minimization. This has been shown to be efficient in balancing several factors in studies with a small sample size, as balance is achieved for each factor separately, instead of for the combination of the factors (Borm, Hoogendoorn, den Heijer, & Zielhuis, 2005; Scott, McPherson, Ramsay, & Campbell, 2002). The following two minimization factors will be used:

- Dose of psychostimulant medication (levels: no dose, low dose, high dose)
- ADHDDSM-IV rating scale score Dutch version of this scale (Kooij et al., 2004) (levels: high or low ADHD score)

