## 6. Methods

In the following part, we will describe detailed the whole procedure from beginning till end, including the rationale for the proposed measurements.

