### Overview Performed Measurements

[figure not shown]

During the **screening session** (~ 75 minutes) the inclusion/ exclusion criteria will be assessed (DSM IV interview, fMRI screening interview, age, IQ Test, use of medication, significant medical conditions, participation in therapy, and participation in other clinical trials). Also the following two baseline measurements will be made:

- A first assessment of the severity of ADHD symptoms the ADHD DSM-IV rating scale, which is a widely used instrument for determine the severity of ADHD, fully based on the DSM-IV (American Psychiatric Association, 2000; Kooij et al., 2005).
- To estimate the intelligence, a shortened version of the WAIS-III-NL (Uterwijk, 2005) will be administered; the Vocabulary test (~10 minutes) and the Block Design test (~10 minutes). Validity coefficients for the Vocabulary and Block Design scores relative to the full form are .88 for Verbal IQ and .83 for Performance IQ (Antshel et al., 2007).

After the screening session randomization will be performed. Randomization will be used to avoid bias in the assignment of subjects to treatment, to increase the likelihood that known and unknown factors (expectations of the therapy, motivation etc.) are evenly balanced across treatment groups and to enhance the validity of statistical comparisons across treatment groups. Randomization will be stratified according to ADHD symptom score and IQ score.

An elaborate assessment of the ADHD symptoms will take place during the **pre-training session** (~75 minutes). During this session a neuropsychological assessment and a resting-state fMRI measurement will be completed. The following neuropsychological tests will be used:

Meta-analytic studies of neuropsychological function in ADHD report moderate to large effect sizes a sustained attention deficit in ADHD (Willcutt, Doyle, Nigg, Faraone, & Pennington, 2005). To assess sustained attention we will use the Sustained Attention dots task (SA-DOTS) as well as the Sustained Attention to Response Task (SART). Both tasks have been shown to discriminate ADHD patients from healthy subjects (Marchetta et al., 2008; Slaats-Willemse et al., 2005; Smilek et al., 2010).

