- To assess visuo-spatial working memory we use the NBack task (~10 minutes) (McElree, 2001). We will use a within-subjects design with three conditions: 2-, 3-, and 4-back, administrated in this fixed order.

Finally will assess cognitive interference, as subjects with ADHD usually underperform on tasks that require cognitive interference (Bush, 2011; Bush et al., 1999; Bush et al., 2008; Cubillo et al., 2010; Dickstein, Bannon, Castellanos, & Milham, 2006; Schneider et al., 2010). We will use the Multi-Source Interference Task (MSIT), a task that has

been especially developed such that it reliably and robustly causes very strong interference effects (Bush & Shin, 2006). It has also been shown that the MSIT discriminate ADHD patients from healthy subjects (Bush et al., 2008).

- During the MSIT (~10 minutes) subjects are presented with a visual display of a set of three numbers (0, 1, 2 or 3). They are asked to report, via button press, the identity of the number that differs from the other two numbers. Interference is caused between the value of the target number, the value of the accompanying numbers, the value of the location of the target number, and the location of the hand used to answer.

After the neuropsychological testing the pre-training session continues with a short fMRI scanning session (~20 minutes total), which includes an anatomical scan (~10 minutes) and a resting-state fMRI scan (~8 minutes). This resting-state fMRI scan will serve as a baseline measure to estimate the severity of the ADHD brain pathophysiology. Previous studies have shown that adults with ADHD show decreased coupling of the anterior cingulate cortex with other brain regions in comparison with healthy subjects (Castellanos et al., 2008). Additionally, this fMRI session will have the function of a practice session, during which subjects can get acquainted with the scanner environment, and the researchers who will be present during the later fMRI-neurofeedback training. If subjects are not comfortable in the scanner environment during the practise session they will be excluded from the study at this point.

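### Randomisation precedes the scanner practice session at which patients can still be excluded, so patients may be lost after allocation and before any training

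*Protocol*

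**What the plan says.** Section 6 (Methods) opens by saying that "we will describe detailed the whole procedure from beginning till end", so its order can be read as chronological. Under Overview Performed Measurements the order is as follows.

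1. Screening session: eligibility is checked, including an MRI screening interview, the symptom rating and the IQ estimate.
2. Allocation: "After the screening session randomization will be performed".
3. Pre-training session: neuropsychological tests, then an anatomical and a resting-state scan that also serve as scanner practice. Here "If subjects are not comfortable in the scanner environment during the practise session they will be excluded from the study at this point".
4. First training session, in the second week.

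Section 4 (Randomization procedure) gives the method: "we will apply a restricted randomization technique called sequential balancing, a form of minimization". It justifies this by the importance of balance in so small a sample. Section 3 sets 10 patients per arm and describes the blinding: "This study is a randomized controlled trial (RTC) with blinding of the participants and blinding of all raters". Section 4 (Inclusion Criteria) already requires the absence of claustrophobia.

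**The concern.** The comfort check at the practice scan is in effect an eligibility decision, and it is placed after allocation. A patient removed there has been counted in the minimisation and assigned to an arm, but receives no training and, being out of the study, has no post-training symptom score. Two things are at stake. The first is numbers and balance. With 10 per arm each patient is a tenth of the arm, and the balance achieved at allocation is no longer guaranteed in the patients who are analysed. The second is the possibility that the decision to exclude could be influenced by knowledge of the arm, because the allocation already exists when it is taken.

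**Working it through.** **Sequence.** The finding rests on the order of steps in Section 6: screening, randomisation, practice scan with possible exclusion, training. No text elsewhere in the protocol places randomisation later. The timeline figures in Sections 3 and 6 could not be read in the text available and should be checked against this order. The Withdrawal section lists voluntary departure, safety, unwillingness to cooperate and intercurrent illness. It does not mention exclusion at the practice scan.

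**No figure to reproduce.** The protocol gives no dropout or scanner-intolerance rate and no sample-size derivation. The calculations below only show scale.

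**Inputs.** From the protocol: 20 patients, 10 per arm, two-sided 5% level. Assumed: an exclusion rate p of 2, 5, 10 or 15%, the same in both arms, independent between patients, with no replacement.

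**Formulas.**
- Expected exclusions = 20p.
- P(at least one) = 1 − (1 − p)^20. For example, 1 − 0.95^20 = 0.642.
- P(unequal arms) = 1 − Σ b(k; 10, p)², summed over k = 0 to 10, where b is the binomial probability of k exclusions in one arm.
- P(arms differ by 2 or more) = Σ b(i; 10, p) × b(j; 10, p) over all |i − j| ≥ 2.
- P(differ by exactly one) is the third quantity minus the fourth. At 10%, 0.687 − 0.244 = 0.443.

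| Assumed rate | Expected exclusions | At least one | Arms unequal | Differ by exactly one | Differ by two or more |
|---|---|---|---|---|---|
| 2% | 0.4 | 33% | 30% | 28% | 3% |
| 5% | 1 | 64% | 54% | 43% | 11% |
| 10% | 2 | 88% | 69% | 44% | 24% |
| 15% | 3 | 96% | 75% | 41% | 34% |

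At every rate a difference of one patient is more likely than a larger one.

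**Cost in precision.** The standardised difference d detectable with 80% power solves 0.80 = 1 − F(t; df, δ). Here F is the noncentral t distribution function, t is the 97.5% point of the central t, df = n1 + n2 − 2, and δ = d√(n1·n2/(n1 + n2)). The last column takes 3 further degrees of freedom for the covariates age, sex and IQ.

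| Arms | Unadjusted | Error df reduced by 3 |
|---|---|---|
| 10 v 10 | 1.33 | 1.34 |
| 10 v 9 | 1.37 | 1.39 |
| 9 v 9 | 1.41 | 1.43 |
| 10 v 8 | 1.42 | 1.44 |
| 8 v 8 | 1.51 | 1.54 |

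Losing one patient per arm raises the unadjusted detectable difference by about 6% (1.41/1.33 = 1.06). Losing two per arm raises it by about 14% (1.51/1.33 = 1.14).

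**After the change.** If the practice scan came before randomisation, exclusions after randomisation under this rule would be zero, whatever the rate.

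**The case against.** The strongest reply is that the harm is small and need not be biased. Exclusion happens before any feedback, both arms have the same pre-assessment, and participants are blind. Loss through scanner discomfort is then expected to be unrelated to the arm, and it costs some precision and balance without invalidating the comparison. Screening for claustrophobia makes a low rate plausible. At 2% the expected loss is 0.4 patients. All of this stands.

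A reader might infer more than the documents support, in four ways.

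- *Staff who know the arm select patients.* The protocol names only participants and raters as blind, and the practice scan introduces patients to the researchers who will attend the training. But it does not say who judges comfort, which could be the patient's own report, or whether that person knows the arm at that time. Section 3 also describes allocation as blind, without saying to whom. The route is open but not shown.
- *The minimisation is undone.* Allocation is patient by patient, and one or two losses may loosen balance without destroying it.
- *The arms will shrink unevenly.* They may. At the assumed rates they stay equal with probability 70/46/31/25%.
- *An as-randomised analysis is impossible.* Excluded patients have a screening symptom score, and the post-training rating needs no scanner, so follow-up could be arranged. As written, exclusion from the study means that no such outcome would be collected. An SAP, not shown, could define the analysis set, but it could not supply those outcomes or change when randomisation occurs.

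**Conclusion.** The sequencing weakness is real and follows from the protocol's own order of steps. Patients can be lost between allocation and training, which reduces the 10 per arm and may loosen the minimised balance. How often depends on a rate that the protocol does not give. Over assumed rates of 2 to 15%, the expected loss is 0.4 to 3 of 20 patients, and none is a possible outcome. The probabilities assume equal rates in the two arms and no replacement. The likely consequence is a modest loss of precision and balance, with selection bias a possibility only. It should be fixed because the remedy is so cheap, but it does not by itself invalidate the trial.

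**What to change.** Move randomisation to after the pre-training session and before training session 1. Suggested wording: *Randomisation is performed after the pre-training session has been completed, among patients who remain eligible after the practice scan.* Patients excluded at the practice scan are then never randomised and can be replaced without affecting the minimised allocation. As a further gain, the baseline tests and resting-state scan are obtained before the arm is assigned.

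The cost is one sentence, with the timeline figures brought into line if they show the present order. No visit or measurement is added. The balancing factors (stimulant dose and symptom score in Section 4, IQ in Section 6) are all available from screening, the suggested mental strategies are the same in both arms, and the arm is not needed until training begins.

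If randomisation must stay where it is, the protocol should say that whoever decides on exclusion is unaware of the arm, that these exclusions are reported by arm, whether and how patients are replaced within the minimisation, and whether their post-training symptom rating is still collected.

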### Summary Measurements

#### Pre-Post training

- ADHD symptom score according to the DSM-IV
- Sustained attention score according to SA-DOTS and SART
- Working memory score according to Digit Span and Nback-task
- Anterior cingulate cortex activation connectivity during resting-state fMRI

#### fMRI-neurofeedback training sessions

- Current Motivation according to QCM
- Cognitive interference score according to MSIT
- Anterior cingulate cortex activation level during MSIT/ neurofeedback training
- Mental strategies used during neurofeedback task

### **Withdrawal of individual subjects**

Subjects can leave the study at any time for any reason if they wish to do so without any consequences. The principal investigator can also withdraw a subject if:

- The investigator believes that for safety reasons (e.g. in the presence of adverse events) it is in the best interest of the subject to stop treatment.
- The subject is unwilling to cooperate for reasons not related to the trial treatment.

An intercurrent illness emerges of which the severity, duration, or required treatment violated the conditions of the trial.

Subjects withdrawn from the study for a medical reason will be followed until the adverse events have been resolved.

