### Objectives:

- (1) Primary objective: investigating whether the modulation of the ACC activation level through fMRI-neurofeedback training reduces ADHD symptoms and improves cognitive functioning.
- (2) Secondary objective: investigating if abnormal activation levels of the ACC in ADHD patients play a causal role in ADHD pathophysiology.

**Study design:** Randomized controlled treatment study with blinding of participants.

**Study population:** 20 subjects with ADHD (age > 18, IQ > 100).

**Intervention:** 10 subjects with ADHD receive 6 sessions with fMRI-neurofeedback from the dorsal anterior cingulate cortex, and 10 subjects with ADHD receive 6 sessions with fMRI-neurofeedback from a control region.

**Main study parameter:** ADHD-DSM-IV rating scale (rated blindly).

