**Serious adverse events**

The occurrence of an adverse experience that is fatal, life-threatening, disabling or requires in-patient hospitalization or causes congenital anomaly will be described as "serious" adverse event and would be notified in writing to the Commissie Mensgebonden Onderzoek Regio Arnhem Nijmegen.

All adverse events will be followed until they have abated, or until a stable situation has been reached. Depending on the event, follow up may require additional tests or medical procedures as indicated, and/or referral to the general physician or a medical specialist.

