## 8. Statistical Analysis

**Related to primary objective (1):** Investigate whether fMRI-neurofeedback training reduces ADHD symptoms.

For the ADHD symptom score, the sustained attention measures, the working memory measures, and the fMRI resting state anterior cingulate cortex connectivity several independent 2 x 2- way ANCOVAs (one per outcome measure) will be conducted (two-tailed, significance level is set at 5%) with session (pre-vs. post-treatment) as within-subjects factor, group (fMRI-neurofeedback vs. control neurofeedback) as between-subjects factor, and age, sex and IQ as covariates.

For the cognitive interference measures, and the fMRI anterior cingulate cortex activation level/ connectivity during MSIT several independent 6 x 2- way ANCOVA (one per outcome measure) will be conducted (two-tailed, significance level is set at 5%) with session (number of training session) as within-subjects factor, group (fMRI-neurofeedback vs. control neurofeedback) as between-subjects factor, and age, sex and IQ as covariates.

The influence of current state of motivation on training success will be calculated by computing non-parametric Spearman's rank correlations within each individual patient.

The mental strategies used will be scored and their influence on training success will be evaluated by computing non-parametric Spearman's rank correlations within each individual patient.

**Related to secondary objective (2):** Investigate if the abnormal activation levels in ADHD patients play a causal role in ADHD pathophysiology.

To estimate the influence of the neurofeedback training on the symptoms a measure of change in activation level during the neurofeedback training/ the transfer blocks at the end of the training will be developed. This measure (sessions x subjects) will be correlated with the performance on the MSIT task in the subsequent session within and across the two groups (fMRI-neurofeedback and control neurofeedback).

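### A randomised patient who stops training early has no planned post-training ADHD rating, because the protocol does not separate stopping training from leaving the study

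*Protocol*

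**What the plan says.** **Withdrawal.** Section 6, Withdrawal of individual subjects, says that patients may leave at any time, and adds: "The principal investigator can also withdraw a subject if" one of three conditions is met. The first is a safety ground, worded in terms of ending treatment. The second is "The subject is unwilling to cooperate for reasons not related to the trial treatment". The third is an intercurrent illness incompatible with the trial conditions.

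**Follow-up after withdrawal.** The same section states: "Subjects withdrawn from the study for a medical reason will be followed until the adverse events have been resolved". Section 7, Serious adverse events, adds: "All adverse events will be followed until they have abated, or until a stable situation has been reached". Neither mentions an outcome assessment.

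**Timing of randomisation.** Section 6, Overview Performed Measurements: "After the screening session randomization will be performed". Withdrawals during training therefore concern randomised patients. So does a further exit at the pre-training scan: "If subjects are not comfortable in the scanner environment during the practise session they will be excluded from the study at this point".

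**Outcome and analysis.** The Summary names the ADHD-DSM-IV rating scale, rated blindly, as the main study parameter. Section 6 places the repeat rating in the post-training session, a week after the final training visit. Section 8 analyses it by a two-group ANCOVA "with session (pre-vs. post-treatment) as within-subjects factor".

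**The concern.** The protocol uses one idea, withdrawal, for two different events: a patient stops the scanner training, or a patient leaves the study and its assessments. The first need not entail the second. Because the two are not separated, and the post rating is dated from the last training session, nothing tells the site to obtain a post score from someone who stops after, say, the third session.

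Most questions about missing data can wait for an analysis plan. This one cannot, because it concerns which data are collected. An analysis plan can define populations and imputation, but it cannot supply a rating that was never taken.

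Two things are at stake. If the patients who stop would have fared differently from those who continue, the symptom contrast may be biased. If they would not, the trial still loses patients that it can ill afford at 10 per arm. Section 4, Randomization procedure, itself stresses the importance of balance at this sample size and uses minimisation to obtain it. Post-randomisation loss can erode that balance.

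**Working it through.** The protocol states no power, effect size, SD or dropout rate, so there is no figure of its own to reproduce. The check has two parts.

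**1. Following one patient through the text.**

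- The patient is screened, has the first ADHD rating and is then randomised (section 6, Overview Performed Measurements).
- The patient stops training early on any of the three grounds (section 6, Withdrawal of individual subjects).
- Stated follow-up: adverse events, if the reason was medical. A patient withdrawn for non-cooperation or a non-medical reason has nothing beyond the general adverse event rule in section 7.
- Post rating: tied to the week after the last training session, with no provision for early stoppers.
- Analysis: with two time points, the session-by-group term compares the mean change between arms. A patient without a post score has no change and drops out of that comparison.

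**2. Illustrative size.** Inputs from the protocol: 10 per arm, two-sided 5%, three covariates (age, sex, IQ). Everything else is assumed, and the SD of change is set to 1.

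*Shift in one arm's mean.* If k of 10 patients are lost and their change would have been g SD worse than that of the patients retained, the retained mean differs from the mean of all ten by (k/10) × g.

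| k lost | g = 0.5 | g = 1.0 |
|---|---|---|
| 1 | 0.05 SD | 0.10 SD |
| 2 | 0.10 SD | 0.20 SD |
| 3 | 0.15 SD | 0.30 SD |

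*Precision.* The standard error of the arm difference is √(1/n₁ + 1/n₂).

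- 10 v 10: √(2/10) = 0.447
- 8 v 8: √(2/8) = 0.500
- Ratio: √(10/8) = 1.118, a 12% increase

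*Detectable difference.* For 80% power from a noncentral t with n₁ + n₂ − 2 − 3 degrees of freedom, the detectable standardised difference is 1.34 at 10 v 10, 1.43 at 9 v 9 and 1.54 at 8 v 8.

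*False-positive rate.* This was simulated under no treatment effect with 100,000 runs. Two of 10 patients are removed from one arm only, chosen by a score correlated ρ with their change. The arms are then compared by a two-sided t test without covariates.

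| ρ | Bias | Rejection rate |
|---|---|---|
| 0 | nil | 5.0% |
| 0.3 | 0.10 SD | 5.4% |
| 0.5 | 0.16 SD | 6.5% |
| 1.0 | 0.32 SD | 11.6% |

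**The case against.** The strongest reply is that the text is silent rather than wrong. It does not forbid a post-training rating in a withdrawn patient, and the safety ground speaks of ending treatment, which could be read as leaving assessments in place. The protocol names no analysis set, and one may be defined in an analysis plan that is not shown. The harm needs withdrawals to occur, and nothing says how many are expected. The illustrated shift of 0.1 to 0.2 SD is under half of the 0.447 SD standard error, and the 11.6% rejection rate needs perfect correlation between loss and outcome. Finally, a patient unwilling to cooperate may also refuse another visit.

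Much of this stands and limits the point. It does not remove the gap: no section schedules the rating, and an analysis plan cannot restore it.

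Three stronger readings are tempting, and the protocol does not support them:

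- **That the primary result becomes a comparison of cooperating completers.** No such population is defined, and the non-cooperation ground is limited to reasons unrelated to the trial treatment.
- **That the decision to withdraw is made by people who know the allocation.** Section 3 lists participants and raters as blinded and does not mention the principal investigator. That is silence. Section 5 gives localisation of the feedback region to experienced researchers and does not say that they decide on withdrawal.
- **That cooperation would fall differently by arm because one region responds less well to training.** No section says that responsiveness differs. Section 5 scales the display individually so that its maximum is a realistic target. Poor cooperation arising from the feedback would in any case be treatment-related, and so outside the quoted ground.

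**Conclusion.** The point holds as a gap in outcome collection. Under the protocol as written, a randomised patient who stops training early has no planned post-training ADHD rating, whichever ground applied, and so cannot enter the pre-post comparison. The same is true of a patient excluded at the practice scan.

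The consequence depends on events that the protocol does not quantify. If loss is unrelated to outcome, the cost is precision alone. If it is related and falls on one arm, losing 2 of 10 gives a bias of roughly 0.1 to 0.2 SD under moderate assumptions, with only a small inflation of the false-positive rate. These figures rest on an assumed number lost and an assumed gap or correlation. They illustrate a possible size and are not predictions. The point should be graded as a cheap improvement to data collection. It does not show that the planned comparison is invalid.

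**What to change.** Leave the withdrawal criteria as they are. Make two wording changes in section 6:

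1. In Withdrawal of individual subjects, state that stopping training does not by itself end participation in the assessments, and that only withdrawal of consent does so.
2. In Overview Performed Measurements, offer the post-training session, at least the blinded ADHD rating, to every randomised patient who has not withdrawn consent, at about the time it would originally have been due.

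As described, that session contains the symptom rating and the neuropsychological tests but no scan, so patients who cannot or will not be scanned can still be assessed. The second resting-state scan belongs to the sixth training session and would not be recovered by this change. How these patients enter the analysis can be left to the analysis plan.

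The cost is an already-defined visit of about 75 minutes, or less if only the rating is taken, for each patient who stops early. Some will decline, most likely among those who were unwilling to cooperate. Including patients with less training may dilute the estimated effect slightly.
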